### Study population

Each participating center will enroll approximately 250 consecutive individuals over a 5-year period from 2011 until 2015, totaling 2,450 adult patients with CKD who provide written informed consent. The participating individuals will be monitored for approximately 10 years until death or until ESRD occurs.

The KNOW-CKD will enroll ethnic Korean patients with CKD who range in age between 20 years and 75 years. The CKD stages from 1 to 5 (predialysis), based on the eGFR, is calculated using the four-variable Modification of Diet in Renal Disease (MDRD) equation as follows:

eGFR (ml/min per 1.73 m^2^) = 175 × [serum Cr (mg/dl)] ^-1.154^ × [age]^-0.203^ × [0.742 if female] × [1.212 if black], using serum creatinine concentrations measured at a central laboratory and an assay traceable to the international reference material [12].

Excluded subjects are those who 1) are unable or unwilling to give written consent, 2) have previously received chronic dialysis or organ transplantation, 3) have heart failure (NYHA class 3 or 4) or liver cirrhosis (Child-Pugh class 2 or 3), 4) have a past or current history of malignancy, 5) are currently pregnant, or 6) have a single kidney due to trauma or kidney donation.

We defined and allocated the specific causes of the CKD into four subgroups: glomerulonephritis (GN), diabetic nephropathy (DN), hypertensive nephropathy (HTN), and polycystic kidney disease (PKD). The definition of the subgroup is defined by the pathologic diagnosis, in the event that the biopsy result is available. Otherwise, the subgroup classification depends on the clinical diagnosis. GN is defined by the presence of glomerular hematuria or albuminuria with or without an underlying systemic disease causing glomerulonephritis. The diagnosis of DN is based on albuminuria in a subject with type 2 diabetes mellitus and the presence of diabetic retinopathy. HTN is defined by the patient’s hypertension history and the absence of a systemic illness associated with renal damage. Unified ultrasound criteria [13] will be used to diagnose PKD. The other causative diseases will be categorized as ‘unclassified’.

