### Follow-up

The participating subjects will visit the center according to the follow-up schedule. At each visit, the subjects will undergo scheduled tests; the investigators will review the subjects’ recent medical histories and occurrence of events. We assumed that 10% of the individuals would withdraw from the study and that ESRD or death would develop subsequently in 10% of the subjects annually [18]. Efforts will be made to prevent drop-outs, i.e., providing free medical examinations, frequent telephone calls and dietary education.

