### Statistical methods and plan

The baseline characteristics of the study participants for each subgroup were presented with descriptive statistics using a one-way analysis of variance or Kruskal-Wallis test according to the distribution of continuous variables and a chi-square test or Fisher’s exact test for categorical variables.

To analyze the association of outcome variables, the time-to-event analysis will be used to evaluate primary outcomes, such as renal events (initiation of renal replacement therapy and 50% decline of GFR), CV events (myocardial infarction and ischemic stroke) and death. The Kaplan-Meier curves and the proportional hazard models will serve as major statistical methods for the outcomes. The incidence or mortality rates according to each outcome variable will be calculated for each etiologic group; the incidence ratios will be presented with reference to the diabetic nephropathy subgroup. The effect of exposure on the development of outcomes will be analyzed separately in each group and in the overall groups. The heterogeneity of each relative risk within the KNOW-CKD subcohort will be analyzed using the Cochran Q test or using a shared-frailty model, where time-dependent confounders should be adjusted [19]. The CKD progression will be evaluated using decreased GFR calculations. Because it is common for a patient with CKD to have a non-linear decline in GFR or a prolonged period of non-progression [20], we will assess the longitudinal trajectory of GFR for the individual participants of KNOW-CKD using the Bayesian smoothing technique [21]. If the progression of CKD is steady and linear, the generalized estimating equation will be adopted to compare the slope of the GFR with repeated measurements. The progression of CKD will be supplemented with an event-based analysis, whereby the occurrence of ESRD or the substantial decrease of GFR will be treated as the events of interest.

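### GFR slopes are to be compared by GEE on the sole condition of linear decline, although each eGFR series stops at ESRD or death; slopes will tend to look too shallow, unequally by cause

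*Protocol article*

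**What the plan says.** In the protocol article, Statistical methods and plan, the slope comparison rests on one conditional sentence. The condition is "If the progression of CKD is steady and linear", and the method is that "the generalized estimating equation will be adopted to compare the slope of the GFR with repeated measurements". The condition concerns the shape of the decline only. No working correlation, weighting or link to dropout is stated.

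Three other statements bear on this:

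- Study population: "The participating individuals will be monitored for approximately 10 years until death or until ESRD occurs".
- Follow-up: the assumption that "ESRD or death would develop subsequently in 10% of the subjects annually", next to the assumption that "10% of the individuals would withdraw from the study". Whether the withdrawal figure is a total or a yearly rate is not clear.
- Statistical methods and plan: individual trajectories are assessed "using the Bayesian smoothing technique", because non-linear decline is regarded as common. Also, "The progression of CKD will be supplemented with an event-based analysis", and for the outcomes in general "The Kaplan-Meier curves and the proportional hazard models will serve as major statistical methods for the outcomes".

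**The concern.** Standard GEE uses whatever visits are observed and is consistent in general only if the chance of being observed does not depend on the eGFR values. Here it does, by design. ESRD is reached through low eGFR, and reaching it ends the series. Late visits therefore come mainly from subjects who started high or declined slowly, and the fitted slope is pulled towards no decline. This happens even when every subject's line is exactly straight, which is the case for which the plan reserves GEE.

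The loss is also uneven. Subjects with DN or HTN start much closer to ESRD than those with PKD, so their series are cut earlier and their slopes flattened more. The Background section states the hypothesis that progression differs between causes of CKD, and the bias falls unequally on that contrast.

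**Working it through.** **Plan's own figure.** None is given for the slope comparison. The only design figure, the hazard-ratio power statement under Statistical power estimation, does not bear on it.

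**Inputs from the article**

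- Baseline MDRD eGFR, mean (SD), Table 2: GN 54.9 (30.6), DN 32.7 (17.9), HTN 36.6 (17.4), PKD 67 (33.9).
- Already in stage 4 or 5, Table 2: DN 38.2 + 14.5 = 52.7%; PKD 12 + 4.8 = 16.8%.
- Visits, Table 1: baseline, 0.5, 1, then yearly to 10 years.
- ESRD or death at 10% a year. At a constant rate, 1 - 0.9^5 = 41% have ended by year 5 and 1 - 0.9^10 = 65% by year 10.

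**Assumptions, not in the article.** Mean slopes of -2 to -4.5 ml/min/1.73 m² per year; between-patient slope SD 0 to 2.5; residual SD 4; ESRD reached at eGFR 10 (7 and 15 also tried); death 2% and withdrawal 1% a year.

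**Model.** eGFR at visit j of subject i is b0i + b1i × t_ij + e_ij, an exact straight line plus noise. Each series is cut at ESRD, death or withdrawal. GEE with identity link solves Σ D_i′ V_i⁻¹ (y_i - μ_i) = 0 over the observed visits. The true slope is the mean of b1i.

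**Step 1: equal true slopes of -3, exchangeable correlation, ESRD at 10**

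| Slope SD | GN | DN | HTN | PKD |
|---|---|---|---|---|
| 1.5 | -2.76 | -2.37 | -2.45 | -2.83 |
| 2.5 | -2.40 | -1.66 | -1.78 | -2.56 |

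- Without truncation all four causes return -3.0, so truncation is the source.
- The false gap between DN and PKD is 2.83 - 2.37 = 0.46 at SD 1.5 and 2.56 - 1.66 = 0.90 at SD 2.5, with DN appearing slower.
- With no slope variation the estimates are -2.98 to -2.99, essentially unbiased.
- A second simulation of the same kind gave DN -2.78, -2.37 and -2.01 and PKD -2.90, -2.90 and -2.50 at SD 1.0, 1.5 and 2.5. At SD 1.0 the false gap is only 2.90 - 2.78 = 0.12.
- With ESRD at 15 and SD 2.5, DN is -1.50 and PKD -2.50. The direction is the same.
- Independence correlation gives -0.5 to -2.1 across causes. It is too shallow even with no slope variation (-1.5 to -2.1).

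**Step 2: unequal true slopes, exchangeable correlation.** With DN truly -4.5 and PKD -3.5 (gap 1.0), GEE gives -3.71 v -3.30 at SD 1.5, a gap of 0.41 in the right order. At SD 2.5 it gives -2.79 v -3.02, the wrong order. Share of runs with the wrong order, 600 per group:

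| True DN v PKD | SD 1.0 | SD 1.5 | SD 2.0 | SD 2.5 |
|---|---|---|---|---|
| -4.5 v -3.5 | 0% | 0% | 33% | 90% |
| -3.5 v -3.0 | 0% | 55% | 99.5% | 100% |

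Under independence the order was wrong in every run of both settings.

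**Step 3: a random-intercept, random-slope mixed model on the same cut data.** With equal slopes of -3, SD 2.5 and ESRD at 10 it gives DN -2.60, HTN -2.66, GN -2.84, PKD -2.90. The false gap between DN and PKD is 2.90 - 2.60 = 0.30, against 2.57 - 1.68 = 0.89 for GEE on those data. For true -4.5 v -3.5 it gives -3.91 v -3.41, so the order returns. When the low eGFR that ends the series is itself recorded, the equal-slope result is DN -2.98 v PKD about -2.93. When it is not recorded, DN is -2.59. A joint model was not computed.

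**The case against.** **The article is silent on detail.** Working correlation, covariates and weights are commonly left to a fuller plan, and weighted GEE would fit the quoted sentence. That much stands. But the article does state when GEE is to be used, and the criterion it states is linearity, which does not protect against this bias.

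**Wrong ranking is not certain.** A reader might infer that causes will be ranked wrongly whenever GEE is used. The documents do not support that. The outcome depends on slope spread, working correlation and true gaps, none of which is given. For true DN -4 v PKD -3, exchangeable GEE kept a gap of 0.90 at SD 1.0 (-3.85 v -2.95) and 0.61 at SD 1.5 (-3.47 v -2.86). At SD 2.5, separate runs ranged from 0.13 in the right order (-2.63 v -2.50) to 0.10 in the wrong one (-2.53 v -2.63). This objection stands in full.

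**The independence results partly reflect an unadjusted model.** With equal slopes and no slope variation, adding baseline eGFR moved DN from -1.04 to -2.95. At SD 2.5 it moved DN only from -0.13 to -1.09. The objection stands in part, since bias remains once slopes vary. The article's own remark about prolonged non-progression makes identical slopes unlikely.

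**Other analyses carry the main conclusions.** GEE is conditional, the main outcomes use time-to-event methods, and the event-based progression analysis counts ESRD as an event. This stands and limits the severity. It does not correct the slope estimates.

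**The sentence does not say that slopes are compared by cause.** True; that is inferred from the hypothesis in the Background and from the planned comparison of the four causes in the Discussion.

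**Conclusion.** The point holds as a moderate one. The criterion for choosing GEE looks at the shape of decline and ignores that low eGFR ends the series. Unweighted GEE then gives slopes that are too shallow, more so in DN and HTN than in PKD, and differences between causes are distorted.

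For a true slope of -3 in every cause under exchangeable correlation, DN is understated by about 3.0 - 2.8 = 0.2 to 3.0 - 1.7 = 1.3 ml/min/1.73 m² per year, and PKD by about 0.1 to 0.5, as slope SD goes from 1.0 to 2.5. The size rests on the assumed slopes, slope spread, ESRD threshold and working correlation. The direction did not change with the threshold.

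A reader might go further and conclude that the study's hypothesis will be answered wrongly. That does not follow: reversal is possible rather than assured, and the time-to-event and event-based analyses are not affected by this mechanism.

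**What to change.** In Statistical methods and plan, replace GEE for the slope comparison with a linear mixed model with subject-level random intercept and slope and a time-by-cause term. Because that model alone leaves some bias, add a joint (shared-parameter) model for eGFR and time to ESRD or death, either as the main analysis or as a pre-stated sensitivity analysis. If GEE is kept, weight each visit by the inverse probability of still being under observation given prior eGFR, and label the analysis secondary.

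The cost is a change of wording and some extra programming, with no new data. The drawback is that a distribution for the random effects must be assumed.

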### Results on interim analysis

From July 2011 to September 2013, we enrolled 1,470 participants, including 543 GN, 317 DN, 294 HTN, 249 PKD sub-participants and remaining participants with unclassified subtypes. The baseline demographics and the laboratory values of KNOW-CKD are summarized in Tables 2 and 3. The mean age of the total CKD cohort at the time of study enrollment is 53.6 ± 12.3 years, 38.7% are female, and 31.6% diabetic. The proportion of each CKD stage is as follows; 10.9% (stage 1), 17.2% (stage 2), 18.2% (stage 3a), 22.3% (stage 3b), 23.7% (stage 4) and 7.6% (stage 5, nondialyzed). GN, DN, HTN and PKD were the most common causative diseases in descending order. At baseline, 7.3% of the cohort had a history of coronary heart disease, 8.5% had cerebrovascular disease, and 90.6% had hypertension. In terms of the Charlson comorbidity score and various cardiac parameters, the DN subgroup exhibited the worst profiles (Figure 1 and Table 2). In subjects with advanced CKD stages, the elevated levels of pulse pressure, serum phosphorus, and intact PTH were more pronounced than the subjects with early stages. Hemoglobin levels, 25D and 1,25D, were significantly lower and the left ventricular mass index (LVMI), coronary calcium score and valve calcification were higher in subjects with advanced CKD stages.

**Table 2 T2:** General characteristics of study subjects participating in KNOW-CKD from 2011 to September, 2013

	**Total cohort**^**1**^	**Subcohort**				
		**GN**	**DN**	**HTN**	**PKD**	**p-value**^**2**^
Total participants from 2011 to 2013	**1470**	**543**	**317**	**294**	**249**	
Age	53.6 ± 12.3	50 ± 12.3	59.2 ± 9.3	59.6 ± 10.9	46.9 ± 10.4	< 0.001
Female	569 (38.7)	228 (42)	104 (32.8)	82 (27.9)	127 (51)	< 0.001
BMI (kg/m^2^)	24.4 ± 3.4	24.2 ± 3.4	25.2 ± 3.2	24.8 ± 3.5	23.5 ± 3.1	< 0.001
Waist-Hip ratio	0.89 ± 0.07	0.88 ± 0.07	0.92 ± 0.05	0.9 ± 0.07	0.88 ± 0.06	< 0.001
SBP (mmHg)	127.7 ± 16.5	123.2 ± 14.9	135.8 ± 18.7	127 ± 16.4	128 ± 13.5	< 0.001
DBP (mmHg)	76.6 ± 11.1	75.2 ± 10.6	76.1 ± 11.8	76.8 ± 11.6	79.8 ± 10.2	< 0.001
Pulse Pressure (mmHg)	51.1 ± 12.1	48 ± 10.6	59.7 ± 12.9	50.2 ± 11.5	48.2 ± 9.5	< 0.001
CKD stage 1	160 (10.9)	81 (14.9)	4 (1.3)	2 (0.7)	63 (25.3)	< 0.001
2	253 (17.2)	117 (21.5)	18 (5.7)	18 (6.1)	79 (31.7)	
3a	268 (18.2)	111 (20.4)	45 (14.2)	67 (22.8)	35 (14.1)	
3b	328 (22.3)	110 (20.3)	83 (26.2)	91 (31)	30 (12)	
4	349 (23.7)	93 (17.1)	121 (38.2)	95 (32.3)	30 (12)	
5	112 (7.6)	31 (5.7)	46 (14.5)	21 (7.1)	12 (4.8)	
Creatinine (mg/dL)	1.88 ± 1.17	1.67 ± 1.08	2.48 ± 1.38	2.12 ± 1.00	1.40 ± 0.98	< 0.001
Cystatin C (mg/L)	1.81 ± 0.95	1.61 ± 0.89	2.37 ± 0.99	2.04 ± 0.83	1.34 ± 0.79	< 0.001
eGFR (mL/min/1.73 m^2^)						
MDRD	48.6 ± 29.4	54.9 ± 30.6	32.7 ± 17.9	36.6 ± 17.4	67 ± 33.9	< 0.001
CKD-EPI cr (2009)	51.4 ± 30.3	58.3 ± 31	34 ± 19.5	37.9 ± 17.7	71.8 ± 33.6	< 0.001
Comorbid disease						
Coronary artery disease	107 (7.3)	22 (4.1)	44 (14.1)	32 (10.9)	3 (1.2)	< 0.001
Peripheral vascular disease	22 (1.5)	2 (0.4)	10 (3.2)	9 (3.1)	0 (0)	< 0.001
Cerebrovascluar disease	125 (8.5)	21 (3.9)	37 (11.9)	34 (11.6)	29 (11.6)	< 0.001
Diabetes	462 (31.6)	56 (10.4)	317 (100)	61 (20.7)	3 (1.2)	< 0.001
Hypertension	1325 (90.6)	470 (86.9)	302 (96.8)	283 (96.3)	213 (85.5)	< 0.001
Chronic heart failure	15 (1)	3 (0.6)	8 (2.6)	4 (1.4)	0 (0)	0.011
Arrhythmia	31 (2.1)	8 (1.5)	6 (1.9)	12 (4.1)	3 (1.2)	0.049
Cardiac parameters						
AAC score	1.2 ± 2.6	0.7 ± 1.9	2.6 ± 3.7	1.3 ± 2.7	0.3 ± 1.3	< 0.001
Mean baPWV (cm/s)	1525.0 ± 342.5	1396.4 ± 245.8	1819.2 ± 418.2	1569.1 ± 297.7	1392 ± 213.2	< 0.001
LVMI (g/m^2^) (Echocardiography)	95.0 ± 28.4	89.5 ± 25.2	106.5 ± 30.7	100.6 ± 31.9	85.9 ± 20.1	< 0.001
Coronary Ca score	191.7 ± 569.6	91.6 ± 409.9	496.3 ± 864.6	195.6 ± 569.5	28.5 ± 133.1	< 0.001
Troponin T (ng/mL)	0.016 ± 0.018	0.011 ± 0.010	0.030 ± 0.030	0.016 ± 0.011	0.008 ± 0.004	< 0.001
Valve calcification (Echocardiography)	262 (18.5)	105 (20.2)	82 (27.1)	65 (23)	7 (2.8)	< 0.001

^1^Total participants included those in 4 subgroups and the other unclassified kidney diseases.

ANOVA or Kruskal-Wallis test for continuous variables and Chi-square or Fisher’s Exact test for categorical variables.

Numbers denote mean ± s.d. or number (%).

*Abbreviations:* GN, glomerulonephropathy; DN , diabetic nephropathy; HTN, hypertensive nephropathy; PKD, autosomal dominant polycystic kidney disease; AAC, abdominal aorta calcification; baPWV, brachial-to-ankle pulse wave velocity; LVMI, left ventricular mass index.

**Table 3 T3:** General characteristics of study participants according to CKD stage, KNOW-CKD from 2011 to September, 2013

**CKD Stage**^**1**^							
	**Stage 1**	**Stage 2**	**Stage 3a**	**Stage 3b**	**Stage 4**	**Stage 5**	**p-value**^**2**^
Total participants from 2011 to 2013	**160**	**253**	**269**	**328**	**350**	**112**	
Age	42.2 ± 11.8	49.6 ± 11.9	54.8 ± 11.7	56.7 ± 10.7	57.5 ± 11	54.5 ± 11.6	< 0.001
Female	82 (51.3)	92 (36.4)	79 (29.4)	126 (38.4)	133 (38)	57 (50.9)	< 0.001
Height (cm)	165.4 ± 8.0	166.3 ± 8.5	165.3 ± 8.2	163.5 ± 8.1	164.1 ± 8.3	162.0 ± 8.8	< 0.001
Weight (kg)	64.9 ± 12.8	68.0 ± 12.5	67.6 ± 11.5	66.3 ± 10.5	65.8 ± 11.4	63.6 ± 12.1	0.005
BMI (kg/m^2^)	23.6 ± 3.7	24.5 ± 3.5	24.7 ± 3.3	24.8 ± 3.2	24.4 ± 3.3	24.2 ± 3.5	0.001
Waist-Hip ratio	0.87 ± 0.06	0.88 ± 0.07	0.89 ± 0.07	0.91 ± 0.07	0.91 ± 0.06	0.89 ± 0.06	< 0.001
SBP (mmHg)	126.3 ± 15.6	126.1 ± 16.1	126.3 ± 15.3	126.1 ± 15.3	129.4 ± 17.3	136.1 ± 19.8	< 0.001
DBP (mmHg)	77.6 ± 10.9	77.2 ± 11.9	76.6 ± 10.1	75.5 ± 10.4	76.1 ± 11.7	78.7 ± 11.8	0.275
Pulse Pressure (mmHg)	48.7 ± 10	48.9 ± 10.3	49.7 ± 11.8	50.5 ± 12.3	53.3 ± 12.5	57.4 ± 14.2	< 0.001
Urine ACR (mg/g cr)							< 0.001
A1 (< 30)	53 (34.4)	71 (29.6)	41 (16.3)	37 (12.1)	15 (4.5)	2 (1.9)	
A2 (30 ~ 300)	47 (30.5)	76 (31.7)	86 (34.3)	110 (35.8)	98 (29.5)	20 (18.5)	
A3 (300≤)	54 (35.1)	93 (38.7)	124 (49.4)	160 (52.1)	219 (66)	86 (79.6)	
Primary kidney disease							< 0.001
GN	81 (51)	117 (46)	111 (41)	110 (34)	93 (27)	31 (28)	
DN	4 (3)	18 (7)	45 (17)	83 (25)	121 (35)	46 (41)	
HTN	2 (1)	18 (7)	67 (25)	91 (28)	95 (27)	21 (19)	
PKD	63 (39)	79 (31)	35 (13)	30 (9)	30 (9)	12 (11)	
Unclassified	10 (6)	21 (8)	11 (4)	14 (4)	11 (3)	2 (2)	
Comorbid disease							
Coronary artery disease	4 (2.5)	7 (2.8)	24 (9)	30 (9.2)	36 (10.4)	6 (5.4)	< 0.001
Peripheral vascular disease	1 (0.6)	2 (0.8)	4 (1.5)	1 (0.3)	13 (3.7)	1 (0.9)	0.010
Cerebrovascluar disease	4 (2.5)	13 (5.2)	29 (10.9)	30 (9.2)	40 (11.5)	9 (8.1)	0.004
Diabetes	19 (11.9)	46 (18.3)	73 (27.3)	118 (36.3)	156 (45)	50 (45)	< 0.001
Hypertension	126 (78.8)	217 (86.1)	241 (90.3)	305 (93.8)	331 (95.4)	105 (94.6)	< 0.001
Congestive heart failure	0 (0)	0 (0)	1 (0.4)	3 (0.9)	10 (2.9)	1 (0.9)	0.007
Arrhythmia	1 (0.6)	5 (2)	8 (3)	8 (2.5)	7 (2)	2 (1.8)	0.701
Creatinine (mg/dL)	0.71 ± 0.14	1.00 ± 0.18	1.33 ± 0.18	1.75 ± 0.27	2.68 ± 0.61	4.75 ± 1.36	< 0.001
Cystatin C (mg/L)	0.76 ± 0.15	1.00 ± 0.20	1.33 ± 0.24	1.76 ± 0.33	2.60 ± 0.52	3.89 ± 0.70	< 0.001
eGFR (mL/min/1.73 m^2^)							
MDRD	109.4 ± 20.2	73 ± 8.6	52.1 ± 4.4	37 ± 4.2	23.2 ± 4.3	11.8 ± 2.3	< 0.001
CKD-EPI cr (2009)	110.9 ± 10.4	80.7 ± 10.9	55.8 ± 5.5	38.9 ± 4.8	23.8 ± 4.7	11.9 ± 2.5	< 0.001
Hemoglobin (g/dL)	14 ± 1.4	13.9 ± 1.7	13.5 ± 1.8	12.8 ± 1.8	11.7 ± 1.5	10.6 ± 1.2	< 0.001
P (mg/dL)	3.5 ± 0.6	3.5 ± 0.6	3.5 ± 0.5	3.6 ± 0.6	3.9 ± 0.6	4.7 ± 0.7	< 0.001
hsCRP (mg/L)	1 ± 2.3	1.8 ± 3.9	2.2 ± 6.4	1.7 ± 3	3.1 ± 8.1	1.9 ± 3.8	< 0.001
Intact PTH (pg/mL)	40.2 ± 17.7	38.8 ± 14.2	53.2 ± 30.2	55.7 ± 21	92.4 ± 41.8	220 ± 118.3	< 0.001
25D (ng/mL)	15.8 ± 4.8	18.9 ± 6.7	19.3 ± 7.7	18.7 ± 7.3	18.2 ± 8.2	17.1 ± 7.8	< 0.001
1,25D (pg/mL)	30.5 ± 7.6	30.8 ± 7.3	28.5 ± 7.5	26.9 ± 5.8	23.5 ± 5.3	24.7 ± 7.4	< 0.001
Cardiac parameters							
Mean baPWV (cm/s)	1313.4 ± 189.3	1419.4 ± 239.4	1502 ± 303.6	1587 ± 329.4	1637 ± 417.6	1629.8 ± 369.2	< 0.001
LVMI (g/m^2^) (Echocardiography)	85.5 ± 23	86.2 ± 23.1	89.9 ± 23.9	96.1 ± 25.2	104.1 ± 31.2	109.6 ± 39.6	< 0.001
Coronary Ca score	44.2 ± 225.7	101.1 ± 313.1	230.7 ± 705.3	219.5 ± 599.1	252.9 ± 634.9	241.9 ± 644.6	< 0.001
Troponin T (ng/mL)	0.006 ± 0.003	0.008 ± 0.004	0.011 ± 0.006	0.016 ± 0.015	0.024 ± 0.024	0.031 ± 0.030	< 0.001
Valve calcification (Echocardiography)	12 (7.6)	31 (12.6)	39 (15.3)	75 (23.5)	75 (22.5)	30 (28)	< 0.001

^1^CKD stage classified by MDRD equation.

ANOVA or Kruskal-Wallis test for continuous variables and Chi-square or Fisher’s Exact test for categorical variables.

Numbers denote mean ± s.d. or number (%).

*Abbreviations:* GN, glomerulonephropathy; DN, diabetic nephropathy; HTN, hypertensive nephropathy; PKD, autosomal dominant polycystic kidney disease; baPWV, brachial-to-ankle pulse wave velocity; LVMI, left ventricular mass index.

**Figure 1 F1:**
[figure not shown]
**Age-adjusted modified Charlson comorbidity index in total and subgroup participants, KNOW-CKD 2011–2013.** Abbreviations: GN, glomerulonephritis; DN, diabetic nephropathy; HTN, hypertensive nephropathy; PKD, polycystic kidney disease.

## Discussion

The prevalence of CKD is increasing, as are the risk factors for CKD, such as diabetes, metabolic syndrome, and hypertension [22]. The National Health and Nutrition Examination Survey (NHANES) data from the U.S.A. show that the prevalence of CKD increased from 10% in the 1994–1998 cohort up to 13.1% in the 1999–2004 cohort [23].

CKD is a major risk factor for the development of cardiovascular complications and all-cause mortality. One large observational study reported that the risk of death increased dramatically as the GFR decreased below 60 ml/min per 1.73 m^2^[3]. The adjusted hazard ratio for death was 3.2; the eGFR ranged from 15 ml/min to 29 ml/min per 1.73 m^2^.

In a recent meta-analysis of the general population cohort, including a total of more than one million individuals [24], the risk of death was fairly constant at eGFR of 75–105 ml/min per 1.73 m^2^. However, albuminuria, which is the earliest marker of glomerular damage, was independently associated with increased mortality, even in the presence of normal GFR. This point emphasizes the importance of albuminuria as a prognostic indicator, independent of GFR stages. Therefore, unlike previous CKD cohort studies, the KNOW-CKD included subjects with albuminuria or other early markers of kidney damage and with normal or mildly decreased GFR (CKD stage 1 to 2), as well as subjects with GFR < 60 ml/min per 1.73 m^2^ (CKD stages 3 to 5). The KNOW-CKD will also analyze various outcomes of CKD based on the specific causes of CKD and based on the GFR and albuminuria categories.

Many studies have shown that racial/ethnic disparities exist in mortality and cardiovascular outcome among individuals with CKD [25-28]. Asian patients with CKD generally have a lower burden of CV disease compared with other racial groups. The KNOW-CKD, which is the first large-scale cohort study with Korean patients with CKD, aims to explore the course of renal progression and CV events and to elucidate the risk factors for renal or CV outcomes in Korean subjects with CKD.

The original MDRD Study equation [29], which was developed in 1999, was modified for creatinine assays traceable to the international reference material for creatinine [12]. However, the accuracy and the precision of the MDRD equation have been controversial issues, especially at higher GFR. The CKD-EPI equation, which uses the same four variables as the MDRD Study equation, has less bias than the MDRD Study equation [14], especially at GFR > 60 ml/min per 1.73 m^2^, and is suggested to be more accurate than the MDRD formula in Asian populations. The KNOW-CKD will employ the MDRD Study equation [12], as well as the CKD-EPI creatinine [14] and the CKD-EPI creatinine-cystatin C equations [15], to ensure the accuracy of the GFR estimation. Creatinine and cystatin C assays will be conducted in a central laboratory, using assay methods traceable to the international reference materials [16,17].

The KNOW-CKD will evaluate the complication profiles of anemia and mineral-metabolic derangements across the CKD stages. The KNOW-CKD will compare the clinical manifestations and natural course of the following four major renal etiologic subgroups: GN, DN, HTN, and PKD. Various biomarkers from the serum and urine samples will be evaluated to determine the risk prediction of adverse consequences. The genetic and epigenetic factors will be targeted. The KNOW-CKD will also evaluate the socio-economic burden and its impact on the quality of life, and the hospitalization of patients with CKD. Comparing the KNOW-CKD with other large-scale CKD cohorts through international collaboration may provide a platform for future research.

